### Objective {7}

Here, we present the protocol of a multicenter, positive-controlled, randomized clinical study investigating the efficacy and safety of Shi-style cervical manipulation therapy for treating acute and subacute neck pain. Our hypothesis is that Shi’s cervical manipulation would have more advantages in efficacy, safety, and satisfaction to treat acute and subacute neck pain than traditional NSAIDs.

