## Methods: participants, interventions, and outcomes

### Study setting {9}

This is an exploratory, multicenter, positive-controlled, randomized clinical study. This trial began in October 2019 and ends in October 2021. It is organized and implemented by the Department of Orthopedics and Traumatology of Shuguang Hospital Affiliated with Shanghai University of Traditional Chinese Medicine. The research is planned to be completed in Shuguang Hospital Affiliated with Shanghai University of Traditional Chinese Medicine (Shuguang Hospital for short), Shanghai Jing’an District Central Hospital (Jing’an Center Hospital for short), and Shanghai Xiangshan Hospital of Traditional Chinese Medicine (Xiangshan Hospital for short). Shuguang Hospital is a hundred-year-old hospital in Shanghai. It is a grade III, class A comprehensive hospital of traditional Chinese medicine. It is a national model hospital of traditional Chinese medicine and has three key disciplines of the Ministry of Education. Shi’s orthopedics and traumatology, as one of the key disciplines of the Ministry of Education, has a history of nearly 150 years and is one of the first national intangible cultural hospitals. Jing’an Central Hospital is a grade III, class B general hospital with a history of more than 70 years. It is the teaching hospital of Shanghai Second Medical University, Shanghai University of Traditional Chinese Medicine, and Medical College of Shanghai Tongji University. Xiangshan Hospital is one of the first grade II, class A hospitals of traditional Chinese medicine in Shanghai. It has a history of more than 40 years, which is a hospital of traditional Chinese medicine and integrated traditional Chinese and Western medicine. All three hospitals are responsible for the program’s therapeutic interventions and are located in Shanghai, China, and Shuguang Hospital is the main responsible center of this project. The reasons for choosing these three hospitals as the research centers of this project are as follows, On the one hand, these three hospitals are all located in the center of Shanghai, with dense population and convenient transportation, which is conducive to the treatment and follow-up of the subjects; on the other hand, the orthopedics and traumatology department of these three hospitals is very famous in Shanghai, and Shi’s orthopedics and traumatology department of Shuguang Hospital and the other two hospitals often carry out cooperation in clinical diagnosis and treatment techniques and scientific research. These convenient conditions contribute to the smooth development of this research project. According to the standard implementation method of randomized multicenter clinical trials, patients with neck pain who meet the study standard are randomly divided into trial group and control group (subjects 1:1).

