#### Outcomes {12}

##### Effectiveness evaluation index

The manual intervention program was pre-tested in our research group’s experimental study and was in effect immediately after the shortest treatment, and the longest treatment time was 12 weeks. Combined with the reported literature on related neck pain [14, 15], both groups are treated according to the main intervention methods of each group for a period of up to 12 weeks. Clinical data will be collected before the intervention and immediately after the first treatment; at 3 days and 1, 2, 4, 8, and 12 weeks after the intervention; and at 26 and 52 weeks after treatment follow-up of clinical observation index data collection. The clinical observation indexes are as follows: (1) cervical pain is the primary observation index, measured by NRS [16] and composed by a horizontal line with a length of 0–10 cm, and the anchor words are “0” for “no pain” and “10” for “extreme pain.” Participants are asked to select a point on the NRS line segment that corresponds to their current or recent week’s average pain intensity and draw a vertical line as a marker to express the pain intensity. The researchers determine the NRS score by measuring the distance from the starting point of “painless” to the marker point; the higher the score is, the stronger the degree of pain is. The specific judgment is as follows: 1–3 cm is mild pain, 4–6 cm is moderate pain, and 7–10 cm is severe pain. The secondary indices include the following: (2) cervical dysfunction index, measured by patient self-evaluation with cervical NDI [17, 18], which has 10 items in total, six options under each item, from light to heavy, corresponding to the score of 0–5, the lowest score of each item is 0, and the highest score is 5; the higher the score is, the more serious the degree of dysfunctions. NDI (%) = [(total score)/(number of items completed by subjects × 5)] × 100. The specific judgment is as follows: 0–20% indicates mild dysfunction, 21–40% indicates moderate dysfunction, 41–60% indicates severe dysfunction, 61–80% indicates extremely severe dysfunction, and 81–100% indicates complete dysfunction (whether subjects have exaggerated symptoms should be checked in detail); (3) cervical activity measurement [19], measured by the cervical vertebra mobility measurement program of Android mobile phone system, with a minimum of 5 degrees carry measurement; (4) overall improvement, measured by self-evaluation of patients with SF-36 (The Medical Outcomes Study 36-Item Short-Form Health Survey) [20, 21], which is composed of physical functioning, role-physical, bodily pain, general health, vitality (VT), social functioning (SF), role-emotional, mental health, and health transition; and (5) satisfactory treatment, determined by patient self-evaluation, is 1 of 3 levels: dissatisfied, satisfied, and very satisfied.

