Specific statistical data analysis, using the latest SPSS statistical analysis software, first of all, paired *t* test statistical analysis is carried out for each group’s pre-treatment pain and the improvement of each group’s pain after treatment intervention, and single-factor analysis of variance is carried out for each group’s immediate, 3-day, 1-, 2-, 4-, 12-week pain after intervention; secondly, before treatment and immediately after treatment intervention, 3 days, 1, 2, 4, and 8 weeks. One-way ANOVA is used to analyze the cervical dysfunction index, cervical activity, overall improvement, and treatment satisfaction of patients at 12 weeks. All the statistical tests are double-sided, *P* < 0.05 would be considered statistically significant.

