## Discussion

The purpose of this study is to confirm our hypothesis through clinical trials that Shi’s cervical manipulation has more advantages in the efficacy, safety, and satisfaction of acute and subacute neck pain than traditional NSAIDs.

To achieve the goal of the study, a multicenter, positive-controlled, randomized clinical trial, comparing traditional analgesic drugs (NSAIDs) for neck pain is used to evaluate and show that Shi’s manipulation is more effective, safe, and satisfactory in the treatment of acute and subacute neck pain.

According to the latest survey [1–3], 71.5% of the general population had neck pain for more than a year. Although neck pain caused only 1.7–11.5% of disability, it is worth noting that, equivalent to back pain, it caused a huge burden and disability rate on individuals and the social economy and was listed as 1 of 5 chronic and refractory diseases by the US government. With the continuous development of social life, the high incidence rate of neck pain is not only confined to developed countries such as the USA, but also affects the developing countries, and has become a worldwide urgent disease [22–24]. At present, the clinical treatment of neck pain is no more than surgical treatment and non-surgical treatment [25]. Various clinical case studies confirm that the long-term effect advantage of surgical treatment is very limited compared with non-surgical treatment [26–29]. The latest research shows that clinical management of neck pain should pay close attention to the active diagnosis and treatment of acute and subacute neck pain, in an attempt to and thwart its progression to chronic neck pain [1, 16, 30]. Previous clinical trials have confirmed that Western chiropractic manipulation, health education, family exercise, and drugs are the main non-surgical treatment measures for acute and subacute cervical pain [11, 31–33]. Chiropractic manipulation, which can effectively relieve patients’ neck pain and cervical dysfunction, has both short- and long-term effects with clinical advantages, while drug treatment generally extends the treatment course. Therefore, clinicians should pay more attention to the cost of treatment, adverse drug reactions, and patient acceptance [11, 30, 34].

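### The plan sets out to confirm superiority on satisfaction, a secondary index tested with three others at an unadjusted 0.05, yet calls the study exploratory

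*Protocol article*

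**What the plan says.** All references are to the protocol article.

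- **Role of the outcomes.** Outcomes {12}, under the effectiveness evaluation index, names neck pain on the NRS as the one primary index. It lists four secondary indices: Neck Disability Index (NDI), cervical mobility, SF-36 (called overall improvement) and treatment satisfaction. Sample size {14} is based on the 12-week NRS score.
- **Test rule.** Statistical methods {20a} says "One-way ANOVA is used to analyze the cervical dysfunction index, cervical activity, overall improvement, and treatment satisfaction of patients at 12 weeks" and then "All the statistical tests are double-sided, *P* < 0.05 would be considered statistically significant". It gives no order, alpha split or key secondary outcome.
- **What is to be concluded.** Objective {7} states the hypothesis that manipulation "would have more advantages in efficacy, safety, and satisfaction to treat acute and subacute neck pain than traditional NSAIDs". The Discussion opens with "The purpose of this study is to confirm our hypothesis through clinical trials" and repeats the same three parts. The Abstract's Background also uses the language of confirming.
- **Status of the study.** Study setting {9} says "This is an exploratory, multicenter, positive-controlled, randomized clinical study". The limitations paragraph at the end of the Discussion calls the work a preliminary exploration and leaves full confirmation of effectiveness and safety to follow-up research.

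**The concern.** The document gives two incompatible accounts of its own standing. In one, the trial confirms a three-part hypothesis, one part of which is a secondary outcome. In the other, it is exploratory and confirmation comes later. The test rule settles nothing, because it treats the primary index and every secondary index alike at full alpha.

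What is at stake is the claim that the trial may make. If pain does not differ at 12 weeks but satisfaction or NDI falls below 0.05, nothing in the text stops that result from being presented as confirming part of the hypothesis. The text also does not say whether all three parts must succeed. The Abstract says the results are meant to support wider use of the technique, so the distinction between a confirmed and a suggestive result has practical weight.

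**Working it through.** **Step 1: the passages side by side**

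| Question | One answer | Other answer |
|---|---|---|
| Is the trial confirmatory? | Yes: Abstract and opening of the Discussion | No: Study setting {9} and limitations paragraph of the Discussion |
| Is satisfaction part of the main claim? | Yes: Abstract, {7}, Discussion | No: listed as a secondary index in {12} |
| Is a secondary result below 0.05 a positive finding? | Yes: {20a} calls it significant without qualification | Not as confirmation, if the study is exploratory |

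Each row has support in the text for both answers. If the study is exploratory, the confirming language is wrong. If it is confirmatory for satisfaction, the rule in {20a} does not protect that claim.

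**Step 2: the size on the narrowest reading**

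The plan states no family-wise error rate, so there is no figure of its own to reproduce.

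Inputs:
- per-test level 0.05, two-sided ({20a});
- number of tests m = 4, one per secondary index at 12 weeks, as the sentence in {20a} literally reads;
- all four null hypotheses true;
- equal correlation ρ between the four test statistics. The document gives none, so ρ is an assumption, taken over 0 to 0.8.

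Independent tests: 1 − (1 − 0.05)^4 = 1 − 0.8145 = 0.1855, or 18.5%.

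Correlated tests: with c = 1.96 and U standard normal, the chance of at least one false positive is

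1 − E{[Φ((c − √ρ·U)/√(1−ρ)) − Φ((−c − √ρ·U)/√(1−ρ))]^4}.

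Numerical integration gives:

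| ρ (assumed) | Chance of at least one false significant secondary result |
|---|---|
| 0 | 18.5% |
| 0.3 | 17.4% |
| 0.5 | 15.6% |
| 0.7 | 13.0% |
| 0.8 | 11.4% |

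The lowest value is still more than twice 5% (11.4 / 5 = 2.3).

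**Step 3: does the remedy control the error?**

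Take NRS at 12 weeks first, then satisfaction at 12 weeks only if NRS is significant, each at two-sided 0.05. If NRS truly does not differ, any false claim must first pass the NRS test, so the chance is at most 5%. If NRS truly differs, only the satisfaction test can give a false claim, again at most 5%. No alpha is taken from the primary.

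**The case against.** The strongest reply is that this is ordinary practice. One primary is named, the trial is sized on it, and secondary outcomes are often tested unadjusted below a single primary. Handling of secondary multiplicity is commonly left to an analysis plan, which is not shown here. That stands as far as it goes: the absence of an adjustment is not the finding, and the primary conclusion is untouched. What remains is what the article does state, namely full significance for every test, a stated aim to confirm a claim that includes a secondary index, and an exploratory label.

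Several stronger readings are tempting, but the documents do not support them:

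- **That the outcomes carry no exploratory label.** The study as a whole is called exploratory in {9} and preliminary in the Discussion. The problem is that this label contradicts the confirming language.
- **That seven visits multiply the tests.** The visit list "secondly, before treatment and immediately after treatment intervention, 3 days, 1, 2, 4, and 8 weeks" is a fragment that ends in a full stop with no outcome or test attached. The sentence that names the test says 12 weeks.
- **That nine SF-36 parts are tested separately.** The outcomes section says of SF-36 "which is composed of physical functioning, role-physical, bodily pain, general health, vitality (VT), social functioning (SF), role-emotional, mental health, and health transition", but {20a} treats overall improvement as one index. Larger test counts rest on assumption.
- **That success on any one of efficacy, safety and satisfaction is enough.** The hypothesis joins the three with *and*. Requiring all three would not inflate the error of the joint claim. The plan also specifies no formal superiority test for safety; {20c} says only that adverse reactions are described and compared.
- **That the plan announces it will report a secondary result as confirmed when pain fails.** It does not say so; the text merely leaves this open. Objective {7} itself states a hypothesis without the language of confirming.

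**Conclusion.** The point holds as a contradiction in the stated text. The Abstract and Discussion aim to confirm superiority on three counts, one of which is a secondary index; {20a} tests all four secondary indices at an unadjusted two-sided 0.05; and {9} and the limitations paragraph call the study exploratory.

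Only the four-test, week-12 count is taken directly from the text: about 11% to 19%, assuming that all four nulls are true, that correlation is equal and lies between 0.8 and 0, and that each ANOVA is a comparison between the arms. The last assumption is needed because {20a} does not say this plainly. A secondary result such as satisfaction therefore cannot be claimed as confirmed under the stated rule. The 12-week NRS conclusion does not depend on this point. The change should be made, but it is a matter of wording and does not alter the design.

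**What to change.** 1. In {20a}, state that only the between-group NRS comparison at 12 weeks supports a confirmatory claim. State that the secondary indices, satisfaction included, are exploratory and will be reported as between-group estimates with 95% confidence intervals.
2. Change the confirming language in the Abstract and the Discussion, and the matching three-part hypothesis in {7}, to agree with this and with the exploratory description in {9}.
3. If the sponsor wants satisfaction to remain in the confirmatory claim, specify instead that it is tested at 12 weeks only after a significant NRS result, and leave the other secondary indices exploratory.

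The cost is a few sentences. No patients, visits or data are added, and the primary test keeps its full alpha. The small downside is that secondary results can no longer be announced as confirmed when the primary comparison fails.

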##### Methods for additional analyses (e.g., subgroup analyses) {20b}

There will be no other additional analyses beyond the main analyses for the primary and secondary outcomes.

##### Methods in analysis to handle protocol non-adherence and any statistical methods to handle missing data {20c}

When the case falls off or the patient’s compliance is poor, the reasons for the fall off and poor compliance shall be entered in the case observation form in detail, and the patient’s understanding and support shall be obtained by contacting the patient as frequently as possible; the evaluation items that can be completed shall be completed, and the last treatment time shall be recorded. The case fall off, the patient’s compliance, and adverse reactions shall be statistically described and compared and evaluated between the groups.

##### Interim analyses {21b}

In the middle of the project, a complete project research operation SOP, investigator manual, and case report form should be reassessed and revised, and work training and summary meetings should be held with detailed training and explanation of the test scheme, research operation SOP, and investigator manual contents. A summary of the enrolment progress, treatment success proportions, adverse events, and protocol deviations will be provided to the Data Safety Monitoring Board members, who are not involved in experimental research and treatment.

##### Plans to give access to the full protocol, participant-level data, and statistical code {31c}

The protocol of the study is publicly available on the website of China Registered Clinical Trial Registration Center with no. ChiCTR1900021371.The datasets generated and/or analyzed during the current study are not publicly available due to China laws on privacy protection but are available from the corresponding author on reasonable request.

#### Oversight and monitoring

##### Composition of the coordinating center and trial steering committee {5d}

This project is under the direct supervision and management of the research team from Shanghai University of TCM. The research team and the special case inspector of Shuguang Hospital, the responsible unit of this project, have established a research supervision WeChat group. The supervisor of Shuguang Hospital and the person in charge of each center have established WeChat working group, and the supervisor can spot check the filling standard of case report form of each center at any time. The person in charge of each subcenter shall establish a WeChat group for the case study, and the case observation doctors of each center shall take real-time photos of the collected cases to the person in charge of each subcenter in the working group of each center on the same day and upload the standard situation of filling in the collected case report form.

##### Composition of the data monitoring committee, its role, and reporting structure {21a}

The Data and Safety Monitoring Board (DSMB) will be composed of a physician, medical statistician, ethicist, orthopedic doctor, radiologist, and clinical manager and will oversee the study throughout the study period. They will review the study activities every 3 months. The committee will review the safety data and clinical efficacy reports and determine whether it is clinically safe to continue the clinical trial. They will report their recommendation to the primary investigator from Shanghai University of TCM.

##### Adverse event reporting and harms {22}

During the test, we should observe whether there are adverse reactions and adverse events, and make records. If there are adverse events, such as adverse effects on patients’ consciousness, feeling, exercise, sleep, blood pressure, pulse, heart rate, respiration, and other normal physiological indicators, cervical fracture, skin damage, spinal cord and vertebral artery injury, gastrointestinal discomfort or ulcer, bleeding, and black stool, the occurrence of adverse reactions shall be recorded in detail on the case observation form, including the time, severity, duration, and treatment measures, and correlation with experimental treatment method shall be analyzed with comprehensive consideration of complications and combined treatment. In case of adverse reactions, the clinical observation physician can decide whether to stop the trial according to patient condition. Patients who stop treatment due to adverse reactions should be tracked and investigated, and the results should be recorded in detail.

##### Frequency and plans for auditing trial conduct {23}

This project is under the direct supervision and management of the research team from Shanghai University of TCM. The research team and the special case inspector of Shuguang Hospital, the responsible unit of this project, have established a research supervision WeChat group. The supervisor of Shuguang Hospital and the person in charge of each center have established WeChat working group, and the supervisor can spot check and audit the filling standard of case report form of each center at any time.

##### Plans for communicating important protocol amendments to relevant parties (e.g., trial participants, ethical committees) {25}

After careful discussion and modification by the project team, the study plan of this project was registered on the website of China Registered Clinical Trial Registration Center and further improved and modified according to the modification opinions provided by the expert team, with approval number ChiCTR1900021371. SOP and investigator’s manual for the research scheme of the project are formulated, and full-time researchers of each clinical research center are trained for the project. Each center is required to strictly follow the SOP and investigator’s manual for the research scheme. The ethics of this trial research scheme was reviewed and approved by China registered clinical trial ethics review committee with approval number ChiECRCT20190068. It was modified and implemented according to the expert’s modification opinions.

##### Dissemination plans {31a}

We plan to disseminate the study results through peer-reviewed journal publications and conference presentations. Study findings will also be shared with relevant clinical and scientific groups.

